### Study procedures

At the first appointment, all participants fill out a questionnaire of the ‘Dutch National Care for the Elderly Program (ZonMw-NPO)’, i.e. the Minimal Data Set (MDS)[14] on functionality and a questionnaire on general health related quality of life, i.e. the short form-36 (SF-36) [15,16].

Subsequently, participants receive detailed information on the study procedures in the diagnostic screening strategy arm or care as usual arm, depending on the random allocation of their GP practices.

After six months the electronic medical files of all participants are searched to document changes in medication status, new diagnoses and use of care during the past six months and participants are asked to fill out again the MRC dyspnoea, MDS and SF-36 questionnaires.

### Screening strategy and care as usual

The diagnostic screening includes the following tests: standardized questionnaire on medical history, symptoms and current drug use (participants are asked to bring their medication containers), physical examination with special attention for the heart and lungs, blood tests, electrocardiogram (ECG), spirometry with pre- and post-bronchodilator measurements and echocardiography including tissue Doppler imaging.

The physical examination is performed by a trained physician in a standardized manner. Venous blood samples are taken and after centrifugation specimens of plasma and cells will be stored at −70 degrees Celsius. The blood tests include measurements of plasma B-type natriuretic peptide measurements (NT-pro-BNP), glucose levels, creatinin levels (with a calculated estimated glomerular filtration rate (eGFR) according to MDRD (modification of diet in renal disease)), haemoglobin and Thyroid-Stimulating Hormone (TSH) levels. A standard 12-lead ECG is recorded by a trained employee of the GPs’ laboratory (Saltro) and classified according to the Minnesota coding criteria by a single cardiologist, blinded to all other test results [17].

The spirometry is also performed by a trained employee of Saltro before and 20 minutes after administration of ipratropiumbromide inhalation with an inhalation chamber, and subsequently read and interpreted by a pulmonologist.

Echocardiography is performed with a mobile echocardiography (Vivid-i) by a trained and experienced cardiac sonographer from Saltro. All echocardiographic images will be stored and interpreted by a single cardiologist who is blinded to all other data.

After every investigation, the participant fills out a visual analog scale (VAS) to measure the burden experienced during the investigation (0 = not burdening at all, 10 = extremely burdening).

All investigations take place in the patient’s general practice office. Every participant in the diagnostic screening group receives all measurements. About two weeks after the investigations, the GP of the participant in the diagnostic screening arm will receive all results, with (preliminary) diagnoses (presence or absence of HF and/or COPD and of other diseases) including a treatment advice. The GP can then initiates or adjusts the treatment according to current clinical guidelines.

In the care as usual group, the participating GP only receives the answers to the questionnaires about symptoms (answers to the MRC dyspnoea and exercise tolerance questionnaires) from the participants. It is up to the GP to decide whether he/she actively starts any investigations or treatment depending on the answers provided.

### Outcome measures

#### HF and COPD

The presence of HF and/or COPD present or absent will be determined six months after the initial investigations by an outcome panel that will evaluate all diagnostic test results and the effect of treatment during six months follow-up.

For the diagnosis of COPD, airflow obstruction with spirometry is a prerequisite and defined as a post-dilatory ratio of the forced expiratory volume in one second (FEV1) to the forced vital capacity (FVC) <0.70 (FEV1/FVC ratio <0.70). To classify the severity of obstruction, the GOLD-criteria [11] will be applied by the panel.

For the diagnosis of HF, the panel applies the criteria of the European Society for Cardiology (ESC) [4]. HF is considered present when participants have suggestive symptoms (i.e. breathlessness at rest or on exercise, fatigue, tiredness, ankle swelling) and signs (i.e. pulmonary rales, raised jugular venous pressure, peripheral oedema, laterally displaced apical beat) in combination with objective echocardiographic evidence of cardiac dysfunction at rest. In participants who use diuretics for hypertension, signs of volume overload could be masked and therefore in these participants signs of fluid overload are not obligatory. Participants classified as HF by the panel will further be classified as systolic HF, heart failure with preserved ejection fraction (HFPEF) or right-sided HF (cor pulmonale).

For systolic HF, participants need to have a left ventricular ejection fraction (LVEF) ≤45%. To diagnose HFPEF, there must be echocardiographic evidence of diastolic structural or functional abnormalities (abnormal left ventricular relaxation or diastolic stiffness), left atrial enlargement or left ventricular hypertrophy (LVH) in combination with a LVEF >45% [18]. Participants with echocardiographically-determined LVH and an indexed left atrial volume of ≥34 ml/m^2^ or tissue Doppler abnormal mitral inflow or pulmonary venous flow profile are also classified as having diastolic dysfunction. In participants with atrial fibrillation (AF) a complete diastolic assessment is not feasible and therefore we consider an elevated indexed LA volume sufficient to classify diastolic dysfunction in participants with AF. Isolated right-sided HF is defined as increased pulmonary artery pressure (calculated systolic pulmonary artery pressure >40 mmHg) and a LVEF >45%.

The panel also assessed the most likely cause of HF based on the information from the investigations of the diagnostic screening.

#### Other diagnoses

Other new diagnoses considered as an explanation of reduced exercise tolerance or dyspnoea are (persisting) asthma, pulmonary restriction, obesity, anaemia, renal dysfunction, thyroid disorders and atrial fibrillation.

For the diagnosis asthma a combination of symptoms (dyspnoea, wheezing, coughing, sputum production), allergy and/or hyperreactivity is needed, and an increase of >12% in forced expiratory volume in one second (FEV1) from pre- to post-dilatory measurements further confirms the diagnosis. The diagnosis of pulmonary restriction is based on a post-dilatory forced vital capacity (FVC) post-dilatory < 80% of predicted, in the absence of a diagnoses of COPD.

Obesity is defined as a body mass index (BMI) above 30 kg/m^2^.

Anaemia is considered present if Haemoglobin (Hb) is below 7.0 mmol/l in women and below 8.0 mmol/l in men aged 65 to 69 years. In patients aged 70 years or over anaemia is present if Hb is below 6.9 mmol/l in men and below 6.8 mmol/l in women.

Renal dysfunction is considered present if the calculated, based on the MDRD formula, eGFR is below 90 ml/min/1.73 m^2^ for men and 80 ml/min/m^2^ for women. Severity of renal dysfunction is divided into 4 stages; mild (GFR between 60 ml/min/1.73 m^2^ and 80 (women) or 90 (men), moderate (GFR between 30 and 59 ml/min/1.73 m^2^), severe disease (GFR between 15 and 30 ml/min/1.73 m^2^) and kidney failure (GFR below 15 ml/min/1.73 m^2^) [19].

Thyroid disorders are divided into hypo- or hyperthyroidism. When the Thyroid-Stimulating Hormone (TSH) level is below 0.35 or above 5.5 mu/l, Free Thyroxin 4 (FT4) will be measured. Hypothyroid disease is considered present when TSH >5.5 mu/l and FT4 <11 pmol/l. Subclinical hypothyroid disease is when TSH >5.5 mu/l, and FT4 within normal limits (i.e. between 11 and 23 pmol/l). Hyperthyroid disease is considered present when TSH <0.35 mu/l and FT4 >23 pmol/l. Subclinical hyperthyroid disease is a TSH <0.35 mu/l and FT4 within normal limits.

Atrial fibrillation is classified according to the Minnesota coding [17].

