### Final diagnosis by the panel

The final diagnoses are set by a joint panel consisting of three members, a cardiologist, a pulmonologist and a GP. Consensus diagnosis by the panel will be our reference test for the diagnosis of COPD and HF, in case of any discongruence with the classification described before. This is an established method in case an irreproachable reference standard is lacking, as is the case for HF [22]. In case of no consensus the majority decision will be used. In analogy with earlier studies, the panel will use all available information from the diagnostic and follow-up results: the latter to include the effect of targeted therapy in the decision whether a disease is present. The reproducibility of the panel diagnoses will be evaluated by re-testing a random sample of 10% by the same outcome panel.

The joint panel evaluation is divided in three steps; step 1 history taking, physical examination, blood tests, ECG and spirometry, step 2 adding NT-pro-BNP and step 3 adding echocardiography and follow-up. After step 1 and 2 the panel gives a percentage (0-100%) of their suspicion for the different outcomes. With this, we can evaluate how the panel reaches their final diagnoses (set at step 3) and which investigations add most in reaching this decision.

The above evaluation is also done individually by a GP, a pulmonologist and a cardiologist, but the procedure is changed slightly by dividing step 3 in two steps whereby step 3 includes only echocardiography and at step 4 the follow-up is included and the final diagnoses are made. We will evaluate this individual approach and compare it with the more time consuming joint panel evaluation.

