### Statistical analyses

The yield of previously unrecognized HF and COPD (and other diseases) will be calculated as a proportion with 95% confidence intervals in both arms of the trial. The absolute difference in yield between the arms will then be calculated together with its 95% confidence interval. We will also calculate how many participants in the diagnostic screening group were initially incorrectly diagnosed with COPD or HF.

The difference in functional health and quality of life between the diagnostic screening and care as usual groups at 6 months will be compared taking into account potential baseline difference of relevant parameters at baseline (ANCOVA), although such differences are expected to be minimal because of the randomization procedure.

Multivariable regression analysis with receiver operating characteristic (ROC) curves and percentages correctly diagnosed participants will be used to analyze which of the test used in the diagnostic screening are most predictive or necessary for setting the diagnosis of HF and COPD in the study group. A multilevel approach is used in the analyses to correct for the fact that we randomized at the GP practice and not at the patient level.

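### Pulmonary restriction is excluded by a COPD diagnosis but not by airflow obstruction, so a participant with low FVC and obstruction whom the panel does not call COPD meets the written definition of restriction

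*Protocol article*

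**What the plan says.** Four parts of the protocol article bear on this.

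- **Other diagnoses** introduces the list this way: "Other new diagnoses considered as an explanation of reduced exercise tolerance or dyspnoea are (persisting) asthma, pulmonary restriction", followed by several non-pulmonary conditions. Restriction rests on a post-dilatory FVC "post-dilatory < 80% of predicted, in the absence of a diagnoses of COPD". That is the only exclusion. Asthma rests on symptoms with allergy and/or hyperreactivity, and "an increase of >12% in forced expiratory volume in one second (FEV1) from pre- to post-dilatory measurements further confirms the diagnosis". The asthma rule contains no FEV1/FVC limit, and asthma does not exclude restriction.
- **HF and COPD** states: "For the diagnosis of COPD, airflow obstruction with spirometry is a prerequisite". Obstruction is defined there on post-dilatory values as "FEV1/FVC ratio <0.70".
- **Final diagnosis by the panel** states: "Consensus diagnosis by the panel will be our reference test for the diagnosis of COPD and HF, in case of any discongruence" with the written classification. A majority decides where there is no consensus, and the panel also uses follow-up and response to therapy.
- **Statistical analyses** states: "The yield of previously unrecognized HF and COPD (and other diseases) will be calculated as a proportion" in each arm, followed by the between-arm difference.

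**The concern.** A low FVC is hard to read as restriction when the airways are obstructed. That is presumably why COPD is an exclusion, although the article gives no reason. If so, the exclusion belongs with the measured obstruction, which the article defines elsewhere, and not with one diagnosis that obstruction may or may not lead to.

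As it stands, two fixed measurements can produce a new diagnosis of restriction or none, depending on a separate judgement about COPD. Any instability in that judgement passes into the restriction count. The plan itself expects some instability, since it re-tests a 10% sample of panel diagnoses. It also expects some recorded COPD labels to be withdrawn, since it will count participants initially misdiagnosed with COPD or HF.

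The effect would not be even across arms. All screened participants have spirometry. In usual care the GP decides whether to test (Screening strategy and care as usual). Cases admitted through this gap would therefore arise mainly in the screening arm and would tend to enlarge the between-arm difference for restriction.

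**Working it through.** The plan states no figure that depends on this definition, so there is nothing to reproduce. The check is to set the rules side by side.

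1. Restriction as written: post-dilatory FVC below 80% of predicted **and** no COPD diagnosis.
2. COPD requires a post-dilatory FEV1/FVC below 0.70. The wording makes this necessary and does not make it sufficient.
3. The panel's decision prevails where it differs from the written classification. An obstructed participant without a COPD diagnosis is therefore possible under the plan's own rules.
4. Combining these:

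| Post-dilatory FVC | Post-dilatory FEV1/FVC | Panel: COPD? | Restriction as written | Restriction if tied to the ratio |
|---|---|---|---|---|
| 80% or more | any | either | no | no |
| below 80% | 0.70 or more | no | yes | yes |
| below 80% | below 0.70 | yes | no | no |
| below 80% | below 0.70 | no | **yes** | **no** |

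A low FVC with a ratio of 0.70 or more and a COPD label should not occur if the prerequisite is kept. Among the rows shown, only the last changes. It needs all three conditions together: low FVC, obstruction, and a decision against COPD. Nothing in the asthma rule keeps an asthma patient out of that row.

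**Possible size (illustration only).** The one relevant count in the documents is recorded asthma in the screening arm in Table 2: 36 of 395, or 9.1%. The share of these 36 in the last row is not given. Assuming 5% to 30%:

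- 36 × 0.05 = 1.8 participants; 1.8 / 395 = 0.5 percentage points
- 36 × 0.30 = 10.8 participants; 10.8 / 395 = 2.7 percentage points

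This is about 2 to 11 people. The base is itself uncertain. The 36 are diagnoses from GP files at selection, some may also carry a COPD label (the overlap is not reported), and newly found asthma or other non-COPD obstruction is not included. Using post-dilatory values should keep the asthma contribution towards the lower end.

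**The case against.** The strongest reply is that the definition is not a mechanical algorithm. The article says the diagnosis is based on the FVC criterion, not that everyone who meets it is counted automatically. A pulmonologist reads each spirogram, with values before and after bronchodilation, and would see the obstruction. The panel section also opens by saying, in general terms, that the panel sets the final diagnoses, and one panel member is a pulmonologist. This stands in part: some or even most such cases may be caught. It does not close the gap. The panel's role as reference test is stated only for COPD and HF, and no text tells the reader or the panel to withhold restriction when the ratio is low.

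A second reply is that this is detail a condensed article leaves to the full protocol. That would answer a complaint about something missing. Here the article states a specific rule, and the rule admits the wrong cases.

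Three stronger readings are tempting, and the documents do not support them:

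- *All obstructed participants without COPD become restriction.* Only those whose FVC is also below 80% of predicted can.
- *Being counted under both asthma and restriction is itself an error.* The article lists possible explanations, does not make them mutually exclusive, and states no rule of one diagnosis per person.
- *The restriction count is inflated by some stated percentage.* That would need the true frequency of restriction as well as the share of affected participants, and neither is given.

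**Conclusion.** The point holds as a minor defect in one outcome definition. As written, participants with low FVC and obstruction whom the panel judges not to have COPD meet the definition of pulmonary restriction, so that component of the yield of other diseases depends partly on the COPD decision. This conclusion rests on the wording alone: obstruction is necessary but not sufficient for COPD, and COPD is the only exclusion.

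The size is unknown and probably small. The range of about 2 to 11 screening-arm participants follows from an assumed share and should not be carried forward as an estimate. The pulmonologist's reading or the panel could reduce the number further. The consequence is confined to restriction. The HF and COPD yield, on which the sample size rests, is unaffected, as are functional health and quality of life.

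**What to change.** For the outcome count, define pulmonary restriction as post-dilatory FVC below 80% of predicted together with post-dilatory FEV1/FVC of at least 0.70, which is the complement of the obstruction cut-off already used under HF and COPD. Report participants with a low FVC, a ratio below 0.70 and no COPD diagnosis as a separate line, so that none disappears from the results.

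This is a one-line change to a definition. It needs no new data, because every screened participant has both values, and it concerns only how outcomes are counted. The small downside is that mixed obstructive and restrictive patterns are not counted as restriction. That is already so for those labelled COPD, and the separate line keeps the others visible. If the intention was always that a ratio below 0.70 means COPD, the change alters no count and only removes the ambiguity.

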#### Functional health

Functional health is measured with the Minimal Data Set (MDS). The dimensions asked in the MDS are: living situation, perceived health and quality of life, health related quality of life (questions of the index EuroQol Five-Dimensional Questionnaire (EQ-5D_index))[20], activities of daily living (ADL) functioning (questions from Katz-15[21]) and health care use (hospital admissions, visits of GP outside office hours, home care and temporally admission to a nursing home).

#### Health related quality of life

Health related quality of life is measured by the SF-36 and the EQ-5D_index (included in the MDS) questionnaires. The SF-36 is divided into nine subscales: physical functioning, social functioning, limitations in usual role activities due to physical problems, limitations in usual role activities due to emotional problems, bodily pain, change in health, general mental health and vitality health change and general health perception. Scores range from 0 and 100.

The EQ-5D_index is a questionnaire with five dimensions (mobility, self-care, usual activities, pain/discomfort and anxiety/depression), which are divided into three degrees of severity, ‘no problem’, ‘some problems’ or ‘major problems’. A single index score can be produced using information from these five dimensions.

Higher scores are associated with a better health related quality of life.

#### Costs

The electronic medical file from the GP is used to collect information about direct costs during the follow-up period of 6 months. Information about GP visits, investigations (i.e. blood tests, ECG, spirometry), outpatient visits, hospitalizations and medication use are collected in both groups. In the diagnostic screening group additionally costs are calculated for all performed test at baseline. Prices will be based on market prices or tariffs.

### Final diagnosis by the panel

The final diagnoses are set by a joint panel consisting of three members, a cardiologist, a pulmonologist and a GP. Consensus diagnosis by the panel will be our reference test for the diagnosis of COPD and HF, in case of any discongruence with the classification described before. This is an established method in case an irreproachable reference standard is lacking, as is the case for HF [22]. In case of no consensus the majority decision will be used. In analogy with earlier studies, the panel will use all available information from the diagnostic and follow-up results: the latter to include the effect of targeted therapy in the decision whether a disease is present. The reproducibility of the panel diagnoses will be evaluated by re-testing a random sample of 10% by the same outcome panel.

The joint panel evaluation is divided in three steps; step 1 history taking, physical examination, blood tests, ECG and spirometry, step 2 adding NT-pro-BNP and step 3 adding echocardiography and follow-up. After step 1 and 2 the panel gives a percentage (0-100%) of their suspicion for the different outcomes. With this, we can evaluate how the panel reaches their final diagnoses (set at step 3) and which investigations add most in reaching this decision.

The above evaluation is also done individually by a GP, a pulmonologist and a cardiologist, but the procedure is changed slightly by dividing step 3 in two steps whereby step 3 includes only echocardiography and at step 4 the follow-up is included and the final diagnoses are made. We will evaluate this individual approach and compare it with the more time consuming joint panel evaluation.

### Blinding

In our single blind study we apply no active measures for blinding the group assignment. The GPs are invited to participate in a study detecting unrecognized HF and COPD. If they agree to participate, their practice is randomized and they receive detailed information. This strategy of selective information is chosen to avoid that GPs in the control group perform all diagnostic tests available in the diagnostic screening program.

Participants will be aware whether their GP practice is allocated to the diagnostic screening arm or to usual care. Researchers are not blinded. There is no risk in observer bias for the outcome, because the questionnaires used to collect outcome measurements are filled out at home by the participants themselves.

### Statistical analyses

The yield of previously unrecognized HF and COPD (and other diseases) will be calculated as a proportion with 95% confidence intervals in both arms of the trial. The absolute difference in yield between the arms will then be calculated together with its 95% confidence interval. We will also calculate how many participants in the diagnostic screening group were initially incorrectly diagnosed with COPD or HF.

The difference in functional health and quality of life between the diagnostic screening and care as usual groups at 6 months will be compared taking into account potential baseline difference of relevant parameters at baseline (ANCOVA), although such differences are expected to be minimal because of the randomization procedure.

Multivariable regression analysis with receiver operating characteristic (ROC) curves and percentages correctly diagnosed participants will be used to analyze which of the test used in the diagnostic screening are most predictive or necessary for setting the diagnosis of HF and COPD in the study group. A multilevel approach is used in the analyses to correct for the fact that we randomized at the GP practice and not at the patient level.

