### Randomization

Primary care practices are randomly allocated to either the diagnostic screening with subsequent targeted intervention strategy or care as usual. Randomization is considered necessary because we aim to quantify the clinical effectiveness of the strategy (test results followed by targeted treatment initiated by the GP). Cluster randomization is used to avoid contamination of GPs and participants between the two groups, which can occur if randomization is performed at an individual participant level.

Randomization is performed by a computer-based program, using the minimization method. Minimization is based on the size of the general practice (number of enlisted men and women) and ensures that the two arms are balanced in the number of participants.

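### Baseline differences are called minimal because of randomization, but Table 2 of the same article shows otherwise, and the baseline adjustment it describes does not extend to the yield comparison (minor)

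*Protocol article*

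**What the plan says.** Protocol article, Statistical analyses: functional health and quality of life at 6 months are compared by ANCOVA that allows for baseline differences in relevant parameters, "although such differences are expected to be minimal because of the randomization procedure". For yield, each arm gets a proportion with a confidence interval, and "The absolute difference in yield between the arms will then be calculated together with its 95% confidence interval". The section closes by saying that "A multilevel approach is used in the analyses to correct for the fact that we randomized at the GP practice" rather than at patient level. No covariate is attached to yield.

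Protocol article, Randomization: "Minimization is based on the size of the general practice", and this is said to be what "ensures that the two arms are balanced in the number of participants". Patient characteristics are not part of the scheme.

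Protocol article, Results of inclusion: 18 practices took part, 8 in the screening arm and 10 in usual care, with 395 and 446 participants. The Sample size section had foreseen around 35 practices. Table 2 gives the baseline characteristics by arm.

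**The concern.** The forecast in Statistical analyses and Table 2 cannot both stand. With few practices and one practice-level factor in the minimization, allocation balances practice size and little else. Patients within a practice resemble each other, so chance differences between arms are larger than under individual randomization.

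The screening arm is older, has fewer men, more osteoarthritis and less known renal insufficiency. For the questionnaires, ANCOVA deals with much of this. For yield, as described, nothing does. Yield counts previously unrecognized disease, so it can depend on age, on sex and on how many participants already carry the diagnosis. A crude difference would then mix case mix with the effect of screening.

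**Working it through.** **Inputs.** Counts, means and SDs from Table 2; 8 and 10 practices from Results of inclusion; intracluster correlation (ICC) 0.05 and a 10-point difference from Sample size. The plan gives that ICC for the diagnosis outcome; using it for baseline characteristics is my assumption, so 0.01 is shown as well.

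**1. The plan's own figures.** Table 2 percentages reproduce: 176/395 = 44.6%, 242/446 = 54.3%; 126/395 = 31.9%, 86/446 = 19.3%; 12/395 = 3.0%, 35/446 = 7.8%. The sample size nearly reproduces: 15% v 5% (5% inferred from the 10-point difference), two-sided 0.05, power 0.80, gives 141 per arm. The design effect 1 + (800/35 − 1) × 0.05 = 2.09 takes this to 296, against the stated 301.

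**2. Standardised differences** (difference divided by the root mean of the two variances).
- Osteoarthritis: 0.126 / 0.432 = 0.29
- Age: 1.6 / √((6.2² + 6.3²)/2) = 1.6 / 6.25 = 0.26
- Renal insufficiency: −0.048 / 0.226 = −0.21
- Male sex: −0.097 / 0.498 = −0.195
- Known HF (5.6% v 4.5%): 0.05; known COPD (17.2% v 14.8%): 0.07

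Of 31 characteristics (age and 30 binary items), 9 exceed 0.10 in absolute value.

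**3. What chance would produce.** Under individual randomization the SD of a standardised difference is √(1/395 + 1/446) = 0.069. With the practices as allocated and ICC 0.05, the design effects are 1 + (395/8 − 1) × 0.05 = 3.42 and 1 + (446/10 − 1) × 0.05 = 3.18. The SD becomes √(3.42/395 + 3.18/446) = 0.126, nearly double. About one characteristic in three would then lie beyond ±0.126 by chance.

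**4. Tests allowing for clustering.** The individual-level z is divided by √(design effect) and referred to t on 18 − 2 = 16 df. With 841/18 = 46.7 per practice, the design effect is 1.46 at ICC 0.01 and 3.29 at ICC 0.05.

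| Characteristic | z | p, ICC 0.01 | p, ICC 0.05 |
|---|---|---|---|
| Osteoarthritis | 4.21 | 0.003 | 0.034 |
| Age | 3.71 | 0.007 | 0.058 |
| Renal insufficiency | −3.03 | 0.023 | 0.11 |
| Male sex | −2.81 | 0.033 | 0.14 |

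**5. Possible shift in HF/COPD yield.** Assumption, not from the documents: underlying yield 15% in both arms.
- Sex: if men carry 1.5, 2 or 3 times the risk, the shift is 0.15/(1 + 0.497(RR − 1)) × (RR − 1) × (0.446 − 0.543) = −0.6, −1.0 or −1.5 points.
- Age: if risk rises 3%, 5% or 10% per year, the shift is 0.15 × (RR^1.6 − 1) = +0.7, +1.2 or +2.5 points.

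The two act in opposite directions if risk is higher with age and in men.

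**6. Possible shift in renal yield.** Let u be the share of participants without known renal insufficiency in whom screening would find renal dysfunction. With all participants as denominator (assumed), those who can still be newly found are 97.0% v 92.2%, so the shift is (0.970 − 0.922) × u = 0.048u. For assumed u of 10%, 30% and 50%, that is 0.5, 1.4 and 2.4 points in favour of screening. The corresponding gaps are 1.1 points for known HF and 2.4 for known COPD.

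**The case against.** The strongest reply is that the clause does no harm where it stands. It is a side remark in a sentence that already commits to ANCOVA, and no analysis rests on it. That is right, and it is the main reason why the point is minor.

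Second, the article is condensed. It does not say that the yield difference will be unadjusted, and the multilevel model may carry covariates that are set out in a fuller document. That also stands: a reader might infer a deliberate decision against adjustment, and the text does not support this. What the article does do is attach baseline adjustment to one set of outcomes and describe the other as a difference in proportions.

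Third, the imbalance may be chance. At ICC 0.05 only osteoarthritis stays below 0.05, without allowance for 31 comparisons. This stands as a description of the table, but it does not rescue the clause: if such differences are ordinary for 18 practices, they should not have been expected to be minimal.

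A reader might also infer that GPs knew their arm when they invited patients, so that the imbalance is recruitment bias. The Blinding section says "If they agree to participate, their practice is randomized and they receive detailed information", but nothing dates the invitations relative to allocation. The GP writes to all eligible frail patients, and participants receive arm-specific information only after the baseline questionnaires. Selective recruitment is possible but not shown.

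**Conclusion.** The point holds, at minor severity. The stated expectation is contradicted by Table 2 and was weakly founded for 18 practices minimized on size alone. The adjustment described covers functional health and quality of life but is not extended to yield.

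The likely consequence for HF/COPD yield is small: known HF and COPD are near balance, and the age and sex scenarios give 0.6 to 2.5 points against a 10-point design difference, partly cancelling. Yield of other diseases is more exposed, because for renal disease the imbalance lies in the diagnosis itself. These sizes rest on the assumed risks shown above; the article holds no outcome data to test them.

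Two stronger readings are not supported. Seven of the 31 characteristics have p < 0.05 in individual-level tests, but those tests ignore the clustering that the plan itself recognizes. And a bias of 0.09 to 0.14 SD against screening in physical function can be produced from age and osteoarthritis, but only with coefficients found nowhere in the documents and for an unadjusted comparison that is not planned.

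**What to change.** Delete the clause that expects minimal differences. Before outcomes are seen, state that the between-arm yield difference will be estimated as a covariate-adjusted (standardised) risk difference within the multilevel approach, adjusting for age, sex, known relevant disease and practice size, the minimization factor. Use the same covariates plus the baseline value of the outcome in the ANCOVA. The crude proportions can still be reported beside the adjusted difference.

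The cost is wording and 1 to 2 of 16 between-practice degrees of freedom for practice size. Age, sex and known disease are already tabulated, practice size was used for the allocation, and the baseline questionnaires are already part of the procedures.
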